## Methods

### Study Design

The study uses a pragmatic, parallel, superiority randomized controlled design, where the intervention condition (the #chatsafe suicide prevention intervention) is compared to a control condition (sexual health content). It will be conducted over an 18-month period with up to a 12-month recruitment period and an 8-week intervention phase.

Participants will be assessed via self-report surveys at 3 time points: time 1 (T1)—baseline; time 2 (T2)—8-week postintervention commencement; and time 3 (T3)—4-week postintervention. In addition, participants will be asked to complete a short weekly survey to monitor safety and allow evaluation of each piece of social media content. All participants will be reimbursed for their time at a rate of Aus $45 (US $31.95) per hour.

The study is being led by researchers based at Orygen and the Centre for Youth Mental Health, University of Melbourne, Melbourne, Victoria, Australia. It will be conducted and reported in accordance with the Consolidated Standards of Reporting Trials statement [14] (Figure 1).

**Figure 1 figure1:**
[figure not shown]
Consolidated Standards of Reporting Trials flow diagram of participants for enrollment, allocation, T1, T2, T3, and analysis stages.

### Participants and Recruitment

Participants will be 400 young people (200 per arm of the trial). Inclusion criteria are being aged between 16 and 25 years, living in Australia, having used social media to communicate about suicide or self-harm *or* having seen suicide- or self-harm–related information on social media, having not previously participated in a research study that was focused on evaluating suicide prevention or sexual health–related content on social media, considering oneself as being an active social media user, and being willing to share one’s mobile phone number with the research team so that one can be contacted with regard to trial-related communications.

Participants will be recruited via social media advertising using Orygen’s social media accounts. Young people who wish to participate will be directed to a brief self-assessment questionnaire to assess eligibility. They will then automatically be directed to a web-based consent form, which explains the key aspects of study involvement and consent process. This is followed by the T1 questionnaire, after which, participants will be randomly allocated to either the intervention group (#chatsafe intervention) or the control group.

The participant flowchart is shown in Figure 1.

### Intervention

The intervention comprises an 8-week social media campaign. Intervention material will take the form of social media posts shared on public Instagram profiles created for the purpose of this study. As shown in Figure 1, the intervention group will receive the #chatsafe suicide prevention content, and the control group will receive the PROSPEct sexual health content. Both groups will receive 24 pieces of content; that is, 3 per week. All content will be delivered to participants’ mobile phones via SMS text messaging via REDCap (Research Electronic Data Capture), an electronic data capture tool hosted at The University of Melbourne. A description of the #chatsafe intervention (group A) is provided in Textbox 1. The content is based on the #chatsafe guidelines and was developed in partnership with young people; examples are provided in Multimedia Appendix 1.

The control content will comprise 8 weeks of sexual health content (PROSPEct content). A description of the control content (group B) is provided in Multimedia Appendix 2, and examples from both the treatment and control conditions are shown in Multimedia Appendix 1.

The intervention content (group A, #chatsafe condition) by week.
**Week 1: introduction**
Co-design—how the campaign was developed in partnership with young peopleCampaign overview: introduction to campaign learning objectivesWhat is safe and unsafe communication about suicide?
**Week 2: have you seen posts on the internet about suicide?**
What is safe and unsafe communication about suicide? (continued)What to do if you’ve seen content that you think is unsafeWhat happens when you report content online?
**Week 3: sharing your own experiences of suicide on social media**
Sharing experiences in a way that is helpful to youSharing experiences in a way that is helpful to othersContent warnings
**Week 4: asking someone if they are feeling suicidal**
Myth busting—it is safe to ask about suicideThings to do before you approach someoneAsking the question
**Week 5: navigating the conversation about suicide**
If they say yes—What you can say to someone in suicidal distress?What to say and do if they say noHow to exit the conversation and looking after yourself
**Week 6: when someone has died by suicide**
Safely sharing the news onlineChecking in on your friends (and yourself)Memorializing the deceased or communicating after the death
**Week 7: helping a friend who has lost someone to suicide**
Checking in with yourselfPlanning how to approach your friendHelpful things to say or do to help a friend affected by suicide
**Week 8: thank you and wrap up**
Available resources and supportsCo-designThank you

### Study Outcomes

The primary outcome is safety when communicating online about suicide, as measured via the purpose-designed #chatsafe online safety questionnaire at T2. This measure was specifically designed for this purpose by 3 study authors (JR, [name], and CC).

Secondary outcomes are (1) confidence when communicating on the internet about suicide, as measured via the purpose-designed #chatsafe online safety questionnaire at T2; (2) willingness to intervene against suicide on the internet, as measured via the Willingness to Intervene Questionnaire at T2 [15]; (3) internet self-efficacy, as measured by the Internet Self-Efficacy Questionnaire at T2 [16]; (4) safety of the weekly #chatsafe content, as measured by the purpose-built weekly evaluation and engagement survey; (5) acceptability of the #chatsafe intervention, as measured by the purpose-built T2 evaluation questions; and (6) safety of the #chatsafe social media intervention (as a whole), as measured by the number of (or absence of) adverse events recorded throughout the trial. Participant adverse events include (1) participant response to item 9 on the 9-item Patient Health Questionnaire [17] at baseline (time 1), time 2, or time 3. (2) Participant response to the 9-item weekly evaluation survey indicates distress, measured by participants selecting “very distressed” in response to the question “To what extent did you find the content this week distressing?” (3) Participant response to the T2 evaluation questionnaire indicates that a particular piece of campaign content made them feel distressed or at risk of suicide. (4) The participant directly contacts the research team via social media or email and reports distress or risk of harm to self. All adverse events will be responded to by the study team, in line with the study’s safety management strategy. (7) Feasibility of the #chatsafe social media intervention was measured by campaign reach via social media analytics, and participant retention or attrition via audit of study enrollment and withdrawal logs. (8) Self-reported evaluations of the acceptability of receiving the #chatsafe social media intervention were measured by purpose-designed study questions. Exploratory outcomes are as follows: (1) subgroup differences (gender, age, previous exposure to, previous experiences of suicide and self-harm, and level of social media usage) at T2 and (2) self-reported open-ended evaluations of the safety, feasibility, and acceptability of receiving the PROSPEct social media intervention for sexual health promotion in the control group at T2.

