## Introduction

### Background

Suicide is the leading cause of death among Australians younger than 25 years, and rates have been increasing over the past 10 years [1]. The pathways that lead a young person to feel suicidal are complex and diverse; however, 1 commonly cited explanation for the recent rise in rates of youth suicide is the impact of social media [2].

Young Australians spend over 3 hours per day on social media, and this sometimes includes communicating with others about their own experiences of suicide and being exposed to suicide-related content posted by others [2-4]. While there are many potential benefits to communicating on the internet about suicide, such as the ability to seek and provide support from others in an accessible and nonstigmatizing manner [3,5], the potential for harm also exists. For example, there are concerns that certain types of content (eg, graphic information or images) may cause distress, lead to imitative suicidal behavior, and have been thought to contribute to suicide clusters [6]. In addition, young people may be exposed to expressions of suicide risk posted by others but feel ill-equipped to respond [7].

Guidelines designed to assist mainstream media outlets to report on suicide in a sensitive manner are widespread and have led to improved safety and quality of communication about suicide [8]. They also appear to be linked to a reduction in suicide rates [9]. However, until recently, no guidelines existed that targeted either social media or young people, who are now creators of their own content.

In response to this, we developed the #chatsafe guidelines [10], which were the first set of guidelines in the world specifically designed to better equip young people to communicate safely on social media about suicide. They were developed using the Delphi consensus method in partnership with young people, media, and suicide prevention professionals [11]. The guidelines consist of five sections: (1) things to consider before you post about suicide; (2) sharing your own thoughts, feelings, or experience with suicidal behavior; (3) communicating about someone you know who is affected by suicidal thoughts, feelings, or behaviors; (4) responding to someone who may be suicidal; and (5) memorial websites, pages, and closed groups.

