
### Outcome Measures

Outcome measures together with the assessment schedule are presented in Table 1. Note that all participants complete the same questionnaires (T1, T2, T3, and purpose-designed 3-item weekly evaluation and engagement survey) regardless of the arm they are allocated to.

**Table 1 table1:** Schedule of assessments and measures.

Measure	Baseline (T1, week 1)	Intervention (weeks 2-9)	Postintervention (T2, week 9)	Follow-up (T3, week 13)
Purpose designed #chatsafe online safety questionnaire	✓	N/A^a^	✓	✓
Patterns of Social Media Use Questionnaire (including 12 items to assess social media usage for the purposes of communicating about suicide and-self harm specifically)	✓	N/A	✓	✓
Perceived Internet-Self Efficacy Scale	✓	N/A	✓	✓
Willingness to Intervene Against Suicide Questionnaire	✓	N/A	✓	✓
Patient Health Questionnaire-9	✓	N/A	✓	✓
Purpose designed 7-items assessing exposure to, and personal experiences of, suicide and self-harm	✓	N/A	✓	✓
Purpose designed 9-item Weekly Evaluation and Engagement survey	N/A	✓	N/A	N/A
Purpose designed 1-item assessing participant reasons for withdrawal/noncomplete	✓	✓	✓	✓
Purpose designed 10-items assessing participants’ evaluations of the intervention content immediately postintervention	N/A	N/A	✓	N/A
Sexual Health Capacity Scale	✓	N/A	✓	✓
Self-Efficacy Protective Sexual Behaviours Scale	✓	N/A	✓	✓
Sexual Health Questionnaire	✓	N/A	✓	✓

^a^N/A: not applicable.

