### Statistical Analysis

At baseline, state of residence, postcode, age, Aboriginal or Torres Strait Island status, gender identity, sexual orientation, primary language spoken at home, cultural background, and educational and occupational background will be reported using descriptive statistics and will be checked for imbalance between trial arms. The moderating effect of gender (male, female, trans, and gender diverse), age group (ie, 16-20 and 21-25 years), time spent on social media, psychological distress, and previous experience of suicide and self-harm will be considered in analyses as covariates.

Analyses will be performed on an intention-to-treat basis, where all individuals randomized will be included in the analysis by their allocated trial arm status regardless of whether they received all, part, or none of the intended treatments. For the primary analysis, we will use linear regression to estimate the difference in the mean changes between the intervention and control arms at T2 in the outcome safety when communicating online about suicide, as measured via the #chatsafe online safety questionnaire. This analysis will adjust for T1 scores. Multiple imputation will be used to address attrition bias, with 50 imputation samples generated using chained equations. We will conduct 2 sensitivity analyses. One sensitivity analysis will be undertaken using complete cases only (ie, repeating the primary analysis but only analyzing participants who have complete T1 and T2 data). The second sensitivity analysis will use multiple imputation and include the following potential moderating factors as covariates: gender (male, female, transgender, and gender diverse), age group (ie, 16-20 and 21-25 years), time spent on social media, psychological distress, and previous experience of suicide and self-harm.

The secondary outcomes at T2 and T3 will be analyzed based on the primary analysis and the 2 sensitivity analyses. We will use linear regression for continuous outcomes, logistic regression for binary outcomes, and negative binomial regression for counts.

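### The adverse-event count that defines whole-intervention safety does not name the suicide and self-harm items collected at T2 and T3, so self-harm reported there may be left out of the safety result

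*Protocol article*

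**What the plan says.** Under Study Outcomes, secondary outcome 6 is the safety of the intervention as a whole, "as measured by the number of (or absence of) adverse events recorded throughout the trial". Four numbered sources follow:

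1. "Participant adverse events include (1) participant response to item 9 on the 9-item Patient Health Questionnaire [17", at T1, T2 or T3. No response threshold is given.
2. "Participant response to the 9-item weekly evaluation survey indicates distress", defined as choosing the very distressed option for that week's content.
3. An answer on the T2 evaluation that ties distress or suicidal risk to one of the posts.
4. "The participant directly contacts the research team via social media or email and reports distress or risk of harm to self".

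Table 1 under Outcome Measures lists a separate instrument, "Purpose designed 7-items assessing exposure to, and personal experiences of, suicide and self-harm", with a tick at T1, T2 and T3. The text above the table says that both arms complete the same questionnaires.

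The analysis text uses this content in one way: "previous experience of suicide and self-harm will be considered in analyses as covariates". Study Outcomes adds previous exposure and experience as an exploratory subgroup factor. Ethical Considerations treats baseline answers as prior risk. It limits later reporting to adverse events that the participant or a team member raises and that are judged possibly attributable to the study.

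**The concern.** The Background says of some suicide-related content that it "may cause distress, lead to imitative suicidal behavior, and have been thought to contribute to suicide clusters". Behavior is thus among the harms that the authors mention for material in this field, and Hypothesis 3 is that the intervention is safe to share. The trial asks both arms about their own experience of suicide and self-harm at two surveys after randomization. The plan nevertheless gives no use for those T2 and T3 answers: they are not named as an adverse-event source, and no between-arm comparison of them is stated.

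At stake is what the safety conclusion can support. A count built mainly on distress, risk and attribution to content could look reassuring while a comparison of reported self-harm, available from the same database and free of attribution, goes unmade.

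**Working it through.** No arithmetic decides this point, and the plan gives no figure to reproduce. The check sets the listed sources against the assessment schedule and the reporting rule.

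| Source | When available | What the participant must do | Names the 7 items? |
|---|---|---|---|
| PHQ-9 item 9 | T1, T2, T3 | Answer a scheduled item; threshold not stated | No |
| Weekly survey | Weeks 2-9 | Rate that week's content as very distressing | No |
| T2 evaluation | T2 only (week 9) | Link distress or suicide risk to a piece of content | No |
| Direct contact | Any time | Approach the team unprompted | No |
| *7-item measure (not listed as a source)* | *T1, T2, T3* | *Answer a scheduled item* | – |

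- **Coverage.** Of the four listed sources, 0 use the 7-item measure.
- **Attribution.** Sources 2 and 3 work only if the participant ties distress or risk to content. Source 4 depends on unsolicited contact. Only source 1 is both scheduled and free of attribution.
- **T3 (week 13).** The weekly survey and the T2 evaluation are not given at T3, so PHQ-9 item 9 is the only scheduled questionnaire source there.
- **Reporting rule.** Ethical Considerations narrows post-baseline reporting to events judged possibly attributable to the study. Randomization and Treatment Allocation says that team members other than the statistician are not blinded, so that judgment may be made with knowledge of the arm. The article does not say who makes it.
- **Path through the gap.** Take a participant who reports self-harm on the 7 items at T2 or T3, whose item 9 answer is not counted, who does not link it to a post and who does not contact the team. None of the four sources then registers an event.
- **Scheduled extent.** Two post-randomization surveys for 400 participants give 2 × 400 = 800 scheduled administrations before attrition. This is the amount of data for which no safety use is stated. It is not a number of missed events.
- **Recall period.** If the items ask about lifetime experience, a participant who answers yes at T1 will normally answer yes again. A later yes would then be informative only among those who answered no at T1. If the items ask about a recent period, the T2 and T3 answers can be compared directly. The article does not say which applies.

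**The case against.** The strongest reply is that the adverse-event list is introduced as what events include, which does not close it. Study Outcomes also points to a safety management strategy, which is in Multimedia Appendix 3 and not shown. A disclosure on a questionnaire may be logged under that strategy, and an article may leave such operational detail to it. Ethical Considerations also has a general route for events raised by participants or the team, not confined to distress. PHQ-9 item 9 and direct contact will probably catch some of the same people. The content of the 7 items is known only from their label, so it is an assumption that they elicit new acts.

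All of this stands as a limit on the claim. It does not remove the point. Study Outcomes defines a declared outcome by naming individual questionnaires and does not name this one, and the analysis section gives the same content a different role. Whatever the appendix says about responding to a disclosure, the article states no by-arm analysis of it.

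A reader might go further and infer that self-harm is excluded from the safety result, or that an excess in the #chatsafe arm could not appear there. The document supports neither, because the list is open and other routes overlap. A reader might also infer that Hypothesis 3 rests on this count alone. It does not: the hypothesis is assessed weekly and at T2, and the safety of weekly content is a separate secondary outcome. Nor does the Background name imitative behavior as the expected harm of #chatsafe posts. It speaks of certain types of content, with graphic material as the example.

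**Conclusion.** The point holds in a limited form. As the article stands, self-harm reported on the 7 items after randomization may be left out of the whole-intervention safety result unless another route captures it, and no between-arm comparison of those reports is stated. The primary efficacy analysis is unaffected.

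The size of the gap cannot be estimated. It depends on the rate of self-harm in this population, on the overlap with PHQ-9 item 9 and on the items' recall period, none of which the document gives. The conclusion assumes that at least some of the personal-experience items ask about the participant's own self-harm, as their label suggests, and that Appendix 3 does not already bring these answers into the outcome. If it does, only the by-arm analysis remains to be specified.

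**What to change.** - **Analysis.** Add to the safety outcome a comparison by arm of self-harm reported on the personal-experience items at T2 and at T3, adjusted for the T1 answer and with no causality filter. The logistic regression already planned for binary outcomes would serve. Report counts and percentages by arm, and the estimate with its confidence interval. With 200 per arm and possibly few events, a nonsignificant difference should not be read as evidence of safety.
- **Wording.** If the items ask about lifetime experience, word the T2 and T3 versions to cover the time since the participant's last survey.
- **Consistency.** Reconcile Study Outcomes, Table 1 and Ethical Considerations so that they state whether these answers count as adverse events and whether the attribution rule applies to them. If they are kept outside the adverse-event count, report the comparison beside it. How to respond clinically to a disclosure is for the sponsor.

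The cost is a few lines of text and possibly one wording change in the survey. No new visit or instrument is needed. If the answers are counted as adverse events, the recorded total may rise in both arms, and the report should explain this.

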### Ethical Considerations

The study has been approved by the University of Melbourne Human Research and Ethics Committee (ID 2022-24238-32907-3). All participants will be required to provide written consent prior to commencement of the study.

The study will be carried out in accordance with the principles contained in the Declaration of Helsinki and the Australian National Health and Medical Research Council (NHMRC) National Statement on Ethical Conduct in Human Research and the NHMRC Australian Code for the Conduct of Research. In addition to being assessed at T2, safety will also be tracked using the weekly evaluation and engagement survey to identify any distress that is attributed to the intervention (see Table 1). Previous distress and suicide risk will be deemed as that reported during the baseline assessment. Further relevant risk will not be reported unless adverse events are reported by the participant or other study team members, which are deemed to possibly having been caused by study activities such as distress because of the intervention or because of interaction with the study team.

As per the pilot study, an SMC has been established. The main purpose of the committee is to oversee the safety of the trial. It comprises the study Chief Investigator (JR), members of the study team, as well as an Orygen Sponsor Operations representative, a statistician, a clinician, and a subject-matter expert. An initial meeting will be held prior to the commencement of recruitment to review the study risk assessment and the determination of safety oversight procedure. The research team will meet fortnightly for the duration of the trial, and a standing function of these meetings will be to review safety incidents and refer any relevant matters to SMC. All members of the SMC will be convened on a study-specific basis (ie, any time a serious safety concern is raised). The SMC will make recommendations as to appropriate risk assessment and mitigation measures, including but not limited to decisions as to whether the study should be amended or put on hold.

Finally, detailed safety protocols have been established and overseen by the trial psychologist (SR) and Orygen’s Sponsor Operations team (Multimedia Appendix 3).

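### The intervention's overall safety outcome counts PHQ-9 item 9 responses given before randomization as adverse events, which conflicts with other sections of the article and would dilute any ratio or any-event comparison of the arms

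*Protocol article*

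**What the plan says.** Study Outcomes defines secondary outcome 6 as the safety of the #chatsafe intervention as a whole, "as measured by the number of (or absence of) adverse events recorded throughout the trial". Four kinds of adverse event follow. The first is "participant response to item 9 on the 9-item Patient Health Questionnaire [17] at baseline (time 1), time 2, or time 3". The others are a top-category distress rating in a weekly survey, distress or suicide risk linked to campaign content in the T2 evaluation, and direct contact with the team reporting distress or risk.

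Participants and Recruitment fixes the order of events: after consent, "This is followed by the T1 questionnaire, after which, participants will be randomly allocated". Table 1 schedules the PHQ-9 at T1, T2 and T3, and Outcome Measures states that "all participants complete the same questionnaires" in either arm.

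Three other places bear on the time window:

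- Aims and Hypotheses, hypothesis 3, has safety assessed weekly during the intervention and at T2. Baseline is not included.
- Ethical Considerations says: "Previous distress and suicide risk will be deemed as that reported during the baseline assessment". Later risk is reported only for adverse events "which are deemed to possibly having been caused by study activities".
- Statistical Analysis says: "The secondary outcomes at T2 and T3 will be analyzed based on the primary analysis and the 2 sensitivity analyses". It assigns "negative binomial regression for counts" without naming the outcomes meant.

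**The concern.** A safety outcome for an intervention should count what happens after people could have been exposed to it. A T1 item 9 response reflects the participant's state at entry. Counting it as an adverse event has two direct consequences. The total is inflated by events that say nothing about the content. And the favourable result the outcome allows for, an absence of adverse events, is out of reach as soon as one participant endorses item 9 at entry. That should be expected, because eligibility requires having communicated about suicide or self-harm on social media or having seen such material there.

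A third consequence depends on how the arms are compared. Pre-randomization events have the same expected number in both arms. On a ratio scale they pull the contrast toward 1, which is the unfavourable direction of error when the question is whether suicide-related content causes distress in people aged 16 to 25.

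**Working it through.** **1. The time window, section by section**

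| Place | Is T1 inside the safety window? |
|---|---|
| Study Outcomes, outcome 6, event type 1 | Yes, named expressly |
| Aims and Hypotheses, hypothesis 3 | No: weekly and T2 |
| Ethical Considerations | No: baseline risk is pre-existing |
| Statistical Analysis, secondary outcomes | Arguably no: T2 and T3 |
| Participants and Recruitment | T1 comes before allocation |

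No section removes T1 responses from the outcome 6 count, so the conflict lies in the article itself.

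**2. Figures available**

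The article gives no item 9 rate, no adverse event rate and no target for outcome 6, so there is no figure of its own to reproduce. It gives 200 participants per arm, 1:1 allocation and a count model that yields a rate ratio. All event rates below are assumptions.

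**3. Item 9 component alone**

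Assume equal endorsement at T1, T2 and T3 in controls, a true post-randomization ratio of 1.5 and full follow-up. Per unit of the control rate:

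- T1 excluded: (2 × 1.5)/2 = 1.50, ln = 0.405.
- T1 included: (1 + 2 × 1.5)/(1 + 2) = 4/3 = 1.33, ln = 0.288.
- Loss on the log scale: 1 − 0.288/0.405 = 29%.

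Other event types reduce this. If they add as many post-randomization events as item 9 at T2 and T3 together, with the same ratio, the result is (1 + 4 × 1.5)/(1 + 4) = 7/5 = 1.40, ln = 0.336, a loss of 17%.

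**4. General form over a range of baseline rates**

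Let b be T1 events per participant, the same in both arms. Let the post-randomization means be 0.20 (control) and 0.30 (intervention).

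- Rate ratio: (0.30 + b)/(0.20 + b).
- Difference in means: (0.30 + b) − (0.20 + b) = 0.10 for every b.
- Poisson standard error of that difference: √[(0.50 + 2b)/200].
- Any-event risk difference, for 20% against 30% and with T1 positivity independent of later events: 0.10 × (1 − b).

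| b | Rate ratio | Difference in means (SE) | Any-event risk difference |
|---|---|---|---|
| 0 (T1 excluded) | 1.50 | 0.10 (0.050) | 10 points |
| 0.1 | 1.33 | 0.10 (0.059) | 9 points |
| 0.2 | 1.25 | 0.10 (0.067) | 8 points |
| 0.3 | 1.20 | 0.10 (0.074) | 7 points |
| 0.5 | 1.14 | 0.10 (0.087) | 5 points |

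**5. Inflation of the tally under the same assumptions**

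Post-randomization events: 200 × 0.20 + 200 × 0.30 = 100. T1 events: 400 × 0.1 = 40 up to 400 × 0.5 = 200. T1 events would then make up 40/140 = 29% to 200/300 = 67% of the reported total.

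**The case against.** The strongest reply is that no biased comparison has been specified. Hypothesis 3 is not comparative, unlike hypotheses 1 and 2, so outcome 6 may be a descriptive tally. The count model is assigned generically and outcome 6 is not named with it. Secondary outcomes are to be analyzed at T2 and T3 on the pattern of the primary analysis, which adjusts for T1; on that reading T1 item 9 never enters an arm contrast. This stands against any claim that the comparison is biased. It does not rescue the definition: outcome 6 carries no time point, runs throughout the trial and names baseline. A descriptive tally would still be inflated.

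A second reply is that Ethical Considerations supplies an attribution rule, and that the list under Study Outcomes is a condensed set of triggers for a safety response, with counting rules held in the safety management appendix, which is not shown. That is possible, and it also means unchanged ideation at T2 or T3 need not be counted again. But the list is given as the content of a measured outcome, and the attribution rule does not amend it.

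Third, item 9 is recorded separately at each time in both arms, so T1 responses can be set aside at analysis and no data are lost. This is correct, and it limits the seriousness of the point.

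A reader might infer that the plan will hide a real excess of harm, or that the ratio necessarily falls to 1.33. The documents support neither. Attenuation requires a ratio or any-event comparison that includes T1, and 1.33 treats item 9 as the only event type, equally frequent at every time.

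**Conclusion.** The outcome definition is wrong as written and conflicts with other parts of the article. It counts pre-randomization responses in the measure of the intervention's safety, which inflates the tally and makes an absence of adverse events unattainable if anyone endorses item 9 at entry. These two conclusions need no assumption about the analysis.

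Dilution of the arm contrast is conditional. It arises for the rate ratio and for the proportion with any event, and not for a difference in mean counts, which loses only precision. Its size cannot be derived from the article. For the item 9 component, a true ratio of 1.5 becomes 1.33 under equal endorsement at each time and full follow-up, and other post-randomization events bring it closer to 1.5. The point concerns one secondary outcome and can be put right with data already planned. It should be settled before analysis, but it does not undermine the trial.

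**What to change.** Reword outcome 6 under Study Outcomes so that only events after randomization are counted, and keep the T1 item 9 response as the participant's baseline value. Bring the wording into line with hypothesis 3, Ethical Considerations and Statistical Analysis. State whether the window closes at T2 or T3, since hypothesis 3 stops at T2 while the event list runs to T3.

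Add a between-arm comparison of item 9 at T2 and T3, adjusted for T1. Counting only new or higher responses, or also modelling the PHQ-9 total, are options for the analysis plan; the correction does not depend on them.

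The change concerns the outcome count only. The team's safety response to any individual item 9 answer, including at T1, is unaffected. The cost is one sentence and one extra regression on data already collected.
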